### Participant recruitment

We estimate that each participating CHC has at least 8000 registered patients with hypertension who have been receiving the regular community hypertension care (i.e., usual care), resulting in more than 32,000 patients being available for this recruitment. Potential participants are identified either through direct PCP referrals or by screening CHCs’ EHRs following three eligibility criteria: (1) age 21 years or older, (2) had uncontrolled BP in the previous 3 months, i.e., ≥140/90 mm Hg; (3) received high school or higher level of education. Eligible participants are first screened over the phone for interest in participation, experience in smart phone and app use, and willingness to provide the consent form. Those who remain eligible are invited to their registered CHC to attend the screening sessions with at least two PCPs and one research electronic engineer who instructs participants on the use of the BP telemonitor and ensures that participants have the appropriate Android or Apple smart phone to download and use the CareLinker app. If the participant has uncontrolled BP, as defined in the above inclusion criterion 5, during the screening visit and signs the consent, the research nurse will continue the procedure by collecting baseline laboratory tests and study questionnaires. The eligible patients will be randomized to the control or to one of the two intervention groups. The recruitment process is expected to take 12 months to complete from September 2016 to September 2017.

### Outcomes

#### Primary outcome measures

The primary endpoint of the trial is changes in mean SBP from baseline (T1) to 12 months (T3) measured using the BP telemonitor (Bliss BL928). The 12 months BP readings will be determined by taking the average of three BP measurements at the follow-up visit to the CHC. All BP data are collected and uploaded simultaneously to the trial database.

#### Secondary outcomes

The key secondary endpoints are changes in mean DBP and hypertension control rate defined as BP <140/90 mm Hg or <130/80 mm Hg (for patients with diabetes or renal diseases) following the national guidelines [21] and changes in measures related to hypertension complications (HbA1C, body mass index (BMI), and lipid levels) from baseline (T1) to 6 months (T2) and 12 months (T3). The other secondary outcome is anti-hypertensive medication adherence, which is assessed by the self-reported, eight-item Morisky Medication Adherence Scale (MMAS) modified to focus on BP drugs at baseline (T1) and 12 months (T3) [20]. These outcomes are measured for the three study groups and compared between the control and intervention groups.

### Sample size and power calculation

The sample size required for this RCT is 330 patients based on the following assumptions. The RCT is powered to detect a clinically meaningful difference in average change between baseline and 12 months SBP of 7 mm Hg and DBP of 5 mm Hg between Group 1and Group 3. We assume that the standard deviation for difference in SBP from baseline to 12 months is 16.5 mm Hg and the difference in DBP from baseline to 12 months is 11.5 mm Hg. Using a two-sample comparison of the mean change between Group 1 and Group 3, a sample size of 88 patients per group is required to have 80% power at the 95% confidence level. This number is further adjusted to 110 per group to account for an estimated dropout rate of 20% during the 12 months follow-up. To reduce this potential dropout, we will provide all participants an additional 2 years of free health consultation services from PCPs and cardiologists as an incentive after they complete the trial. All analyses will be performed according to the intention-to-treat (ITT) principle.

### Randomization process

We use a block randomization design to ensure balance within CHCs and baseline SBP measurements. We set each CHC as a block, and patients are randomized to three groups in each block with a rate of 1:1:1. A study statistician is solely responsible for generating the randomized allocation sequence using computer software (MATLAB version 2014a) and assigning patients to the intervention or control groups. The allocation sequence is concealed in opaque envelopes from all study researchers until the interventions are assigned. Furthermore, an engineer from CareLinker who does not know the grouping information is in charge of training participants of Groups 2 and 3 to use the BP telemonitor and app in order to ensure an equal level of training between the two intervention groups. Due to the nature of the intervention, the study is an open-label trial to all participating patients, physicians, and coordinators at each site.

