## Methods/design

### Study design

The coordinated PCTM study is a 12-month, pragmatic three-arm trial aiming to compare two telemedicine-based hypertension interventions with usual care. Group 1 participants receive usual care (UC) that complies with China’s Hypertension Prevention and Treatment Guideline 2010 (the national guideline) [21]. Group 2 patients additionally receive a BP telemedicine system including a BP telemonitor and a mobile app. Group 3 participants receive all of the above plus coordinated services jointly provided by their PCPs and a designated team of cardiologists who have access to the secure CareLinker website and review patient data with PCPs once every 3 months. PCP-directed proactive interventions such as phone consultations, requests for an immediate clinic visit, or referrals may also be given to Group 3 participants if their relevant PCP receives alerts produced by the CareLinker cloud engine as a result of detecting abnormal BP variability. A total of 330 enrolled patients will be randomized to each group in a 1:1:1 allocation ratio, and all outcome measures will be assessed at baseline (T1), 6 months (T2), and 12 months (T3) throughout the study duration (Fig. 1). We hypothesize that timely healthcare information exchange and closer collaboration between PCPs and cardiologists will improve community BP control. The Standard Protocol Items: Recommendations for Interventional Trials (SPIRIT) checklist is presented in Additional file 1 [22].

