### Setting

This study will be taking place in the XuHui District in Shanghai, China. The four participating community healthcare centers (CHCs) are classified as tier 1 clinics; each has approximately 30–40 practicing PCPs, and they provide a full range of primary care services to nearly 330,000 residents in total. Cardiologists are mainly recruited from Shanghai Chest Hospital, which is located in the same district and is one of the largest chest specialty hospitals in the nation. Potentially eligible patients are identified and referred by PCPs from CHCs, where all data collection will be conducted including baseline and follow-up tests, except for home-based BP telemonitoring.

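### The randomisation is said to ensure balance on baseline SBP but blocks only on health centre, and the analysis does not guarantee adjustment for either

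*Protocol article*

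**What the plan says.** All references are to the protocol article. Under Randomization process the aim is given as: "We use a block randomization design to ensure balance within CHCs and baseline SBP measurements". The next sentence gives the mechanism: "We set each CHC as a block, and patients are randomized to three groups in each block with a rate of 1:1:1". A study statistician produces the computer-generated sequence, and it is concealed in opaque envelopes. No SBP category, SBP-ordered block or minimisation on SBP is mentioned there or elsewhere. The hypertension stages appear twice, under Group 1: usual care (frequency of follow-up) and under Statistical hypothesis, methods, and analyses (subgroups). Neither use concerns allocation.

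The primary endpoint is the change in mean SBP from baseline to 12 months. For its analysis, the statistical section names a linear mixed model with a list of candidate covariates. Baseline SBP stands first and CHC last. Only candidates that prove significantly related to the outcome go into the final model.

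**The concern.** The two sentences on randomisation do not fit together. Blocking on centre controls the arm counts within a centre. It does nothing to make the SBP distribution alike across arms, beyond removing whatever SBP difference exists between centres. The word ensure therefore promises more than the scheme can give.

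Baseline SBP is not an incidental variable here: it is one of the two components of the primary endpoint. A change score depends on where a patient starts, so a chance difference in baseline SBP carries into an unadjusted contrast of changes. Adjustment would remove that, but the plan makes adjustment conditional on a significance test. The same test can drop CHC, the factor on which the allocation is blocked. A reader who trusts the balance claim would think that the design has settled the matter, when the actual protection depends on a data-driven choice.

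**Working it through.** **1. The plan's own figures.** The inputs are an SBP difference of 7 mm Hg, an SD of change of 16.5 mm Hg, 80% power and two-sided 5%.

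- n per group = 2 × (1.960 + 0.842)² × 16.5² / 7² = 87.2, so 88.
- With 20% dropout, 88 / 0.8 = 110 per group, and 3 × 110 = 330.

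These agree with the article. The point concerns allocation and adjustment, not sample size.

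**2. Chance imbalance in baseline SBP.** The arm size of 110 is from the article. The baseline SD is not given and is assumed at 10 to 18 mm Hg. SBP differences between centres are ignored; blocking on centre would remove them and narrow the ranges a little.

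SE of the difference between two arms = SD × √(2/110) = SD × 0.1348. The 95% range is ±1.96 × SE.

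| Assumed SD (mm Hg) | SE | 95% range | P(difference ≥ 3 mm Hg, either way) |
|---|---|---|---|
| 10 | 1.35 | ±2.6 | 2.6% |
| 12 | 1.62 | ±3.2 | 6.4% |
| 15 | 2.02 | ±4.0 | 13.8% |
| 18 | 2.43 | ±4.8 | 21.6% |

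The assumed range can be set against the article's change SD. If baseline and 12-month SDs are equal and their correlation ρ is 0.5 (both assumptions), then SD of change = SD × √(2(1 − ρ)) = SD. The stated 16.5 mm Hg ("standard deviation for difference in SBP from baseline to 12 months is 16.5 mm Hg") then implies a baseline SD of 16.5 and a range of ±1.96 × 16.5 × 0.1348 = ±4.4 mm Hg.

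**3. What an imbalance does if it is not adjusted for.** With equal SDs, a baseline difference d shifts the unadjusted contrast of changes by (1 − ρ) × d in size. For d = 4 mm Hg the shift is 2.0 mm Hg at ρ = 0.5, 0.8 at ρ = 0.8 and 0.4 at ρ = 0.9. The target difference is 7 mm Hg. A difference of 4 mm Hg or more is uncommon: 0.3% at SD 10, 4.8% at SD 15 and 9.9% at SD 18.

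**4. Would the significance screen drop baseline SBP?** Under equal SDs, the correlation of baseline with change is r = −√((1 − ρ)/2). With 3 × 88 = 264 completers, the expected |t| = |r| × √262 / √(1 − r²). The chance of non-significance is about Φ(1.96 − |t|).

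| ρ | r | Expected absolute t | Chance of being dropped | Shift if d = 4 mm Hg |
|---|---|---|---|---|
| 0.5 | −0.50 | 9.3 | about 1 in 10¹³ | 2.0 mm Hg |
| 0.8 | −0.32 | 5.4 | about 0.0003 | 0.8 mm Hg |
| 0.9 | −0.22 | 3.7 | about 0.04 | 0.4 mm Hg |

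So the covariate is at appreciable risk of being dropped only where its omission matters little.

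**The case against.** The strongest reply is that this is a loose sentence with little consequence. Randomisation makes the arms comparable in expectation, and chance imbalance does not bias the comparison. Baseline SBP heads the covariate list, and step 4 shows that it would almost certainly stay. That stands, and it limits the weight of the point. It does not remove the mismatch. The article names its blocking factor, so this is not a detail left to a fuller document, and that factor cannot ensure what the preceding sentence claims. Nor does near-certain retention argue against fixing the covariates in advance: the pre-specified model would usually be the model reached anyway.

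A reader might infer more, and the article does not support it:

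- **Unreliable 1:1:1 within centres.** A block of preset size that fills gives an exact split. That 330 / 4 = 82.5 shows nothing, since equal centres are nowhere stated and 84 + 84 + 81 + 81 = 330 consists of multiples of 3. If a block of 84 stopped at 60 patients, the mean gap between largest and smallest arm would be about 4, but the article documents neither that block size nor such a shortfall. It expects at least 8000 registered hypertensive patients per centre. Block may also be loose wording for stratum, and block sizes are commonly left to the full protocol.
- **Predictable allocation.** One long block is harder to guess than several short ones, and the sequence is concealed in envelopes.
- **A distortion of 2 mm Hg in the primary result.** That needs a 4 mm Hg imbalance together with an unadjusted contrast, which at correlation 0.5 the screen would practically never produce.

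**Conclusion.** The point holds in a limited form. The article states that the randomisation ensures balance on baseline SBP, and the scheme it describes does not do so. The expected scale of chance imbalance is ±2.6 to ±4.8 mm Hg (95%) between two arms of 110, resting on an assumed baseline SD of 10 to 18 mm Hg. Because the primary model retains baseline SBP and CHC only when significant, the stated protection is guaranteed neither by design nor by analysis.

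This is a correction to the text and a free improvement to the analysis, not a threat to the trial's validity. Under equal SDs and 264 completers, baseline SBP would be retained in all but a negligible share of cases at correlations up to about 0.8. For CHC no such reassurance can be calculated, since the article gives no figures on differences between centres. The case for keeping it is simply that the analysis should reflect the factor used in the allocation.

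**What to change.** 1. In Randomization process, delete the claim of balance on baseline SBP. If SBP strata were in fact used, state them and how they were combined with CHC.
2. In Statistical hypothesis, methods, and analyses, pre-specify baseline SBP and CHC as fixed covariates in the primary linear mixed model regardless of significance, and exempt both from the covariate selection rule.

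The cost is one sentence in each place. The article says that the SAP will be finished before database lock, so the second change can be made there. It uses four model degrees of freedom (one for SBP, three for four centres) out of about 264 completers. The sample size stays at 88, 110 and 330. Re-stratifying partway through recruitment is not needed: it would require an amendment and leave two allocation schemes to account for, while fixed adjustment deals with chance imbalance in SBP without either.

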### Group 1: usual care

After enrollment into the study, the UC group (Group 1) patients are managed by their PCPs at the registered CHCs as usual. The healthcare services offered to them comply with the national guideline and include designated follow-ups by PCPs once every 1–3 months for stage 1 (≥140/90 mm Hg) hypertension patients, once every 1 month for stage 2 (≥160/100 mm Hg), and once every 2 weeks for stage 3 (≥180/110 mm Hg) patients [21]. The standard basic measures include blood pressure, fasting blood glucose, serum blood lipids, electrocardiogram (EKG), renal function, weight, and BMI. Patients receiving UC are encouraged to use a logbook to record home BP measurements and present the results during the CHC visit. In addition to medication adjustment or prescription refill, PCPs will review BP trend according to the logbook records or history data in the EHR, provide lifestyle coaching such as dietary, weight management, and physical activity advice, prescribe necessary lab tests, and make referrals to specialists for further treatment of hypertension or comorbidities. PCPs are also responsible for promoting national and regional hypertension management guidelines during each patient encounter. Similar to the intervention groups, UC patients will have three study visits, at baseline (T1), 6 months (T2), and 12 months (T3), to complete study tests and questionnaires.

### Group 2: Intervention, self-management using the telemedicine tool

Patients randomly assigned to this group receive a BP telemedicine system developed by CareLinker Inc. (Shanghai, China) to facilitate BP self-management in addition to all the usual care components. A more detailed description has been reported previously [23]. In brief, the system consists of (1) a BP telemonitor with embedded GSM module that can upload BP readings to the cloud database immediately after the self-measurement; (2) a mobile app that allows patients to manually input healthcare data, display history BP measurements and lab test results, receive personalized lifestyle coaching contents and medication reminders, and communicate with PCPs about hypertension-related health concerns through text messaging.

### Group 3: Intervention, managed in the PCP-Cardiologist Telemedicine Model (PCTM)

Group 3 participants receive all the interventions described above for Groups 1 and 2. In addition, PCPs and cardiologists are provided access to the secure CareLinker website where they can review patient healthcare data including all BP measurements, lab test results, medications in use, and comorbidities if any. They can also use the auto analytics tools of the website to view the BP average, BP trend, and the risk score of each patient developing cardiovascular disease (CVD). The CVD risk scoring was developed according to the published data [24, 25]. Text message alerts of abnormal BP variability detected by the cloud engine will be pushed to the PCPs’ app when they occur, and proactive interventions including phone consultations, medication dosage adjustments, or referrals can be offered to patients. A joint case review session will be set once every 1–2 months for PCPs and partnering cardiologists to exam patients’ disease progresses to determine if further medical treatments need to be administered. The proprietary web-based analytic module also produces automated medication recommendations to PCPs based on each patient’s disease condition.

All patients in Groups 2 and 3 receive proficiency training in using the BP telemonitor and mobile app. PCPs and cardiologists in Group 3 receive training on access and use of the password-protected CareLinker website.

### Data collection and management

The processes of data collection, storage, analysis, display, and delivery are achieved through the interplay of the web server, web application software, General Packet Radio Service (GPRS)-enabled BP telemonitor, and user-end applications (apps) for patients or physicians. All these components are deployed on computer servers owned by and located within CareLinker and operated behind the company firewall.

Patients’ blood pressures are self-measured using the BP telemonitor (Bliss, Shenzhen China), and the readings are encrypted with the GEA4 algorithm and auto-sent to the web server through the mobile network GPRS protocol. The GEA4 is a widely used encryption algorithm published by the European Telecommunications Standards Institute (ETSI). Each BP telemonitor has its unique device ID bound to one patient ID, the change of which is subject only to the clinical trial administrator in the case of device failure. Auto-submitted BP measures by the BP telemonitor help avoid errors or bias that may otherwise occur in the manual input process. Lab tests of HbA1C and blood lipids are performed at baseline and at each follow-up visit, and the blood samples will not be stored. The test results and other medical information are manually recorded into the patient app by research nurses, and error-checked with format, range, and logic rules built into the app before being sent to the web server. An additional designated research staff will proofread all patients’ health information by comparing with the original reports. The study procedure and data collection are detailed in the SPIRIT figure (Additional file 2).

The user-end apps use Hypertext Transfer Protocol over Secure Socket Layer (HTTPS) to communicate data with the web server. At the sender side, the checksum of the data is calculated by the Message-Digest Algorithm (MD5), encrypted by the Data Encryption Standard (DES) algorithm, and sent out through HTTPS. At the receiver side, the received data are decrypted and their checksum is calculated. Only when the checksum of the received data equals to the received checksum, indicating that the data are not modified during the communication and the integrity is verified, are the received data accepted by the receiver. The HTTPS, MD5, and DES are commonly used communication protocols or encryption algorithms for Internet security. Both apps can be operated on mobile devices running Android 3.0/+ or iOS 7.0/+.

The open-source Java Servlet Container Apache Tomcat 8.0 (Apache Software Foundation, [name], USA) is used as the web server, and the web application software is developed on the base of Spring Framework, which is an open-source application framework and inversion of control container for the Java platform. The database uses MySQL 5.7, an open-source relational database management system (RDBMS). Two instances of MySQL configured as master and slave are running simultaneously. The data are automatically synchronized from the master to the slave, and the slave can be auto-switched to perform as the master if the original master fails. Regular backups are carried out to prevent accidental data loss. All patients, PCPs, and cardiologists have their unique IDs, and their login passwords are encrypted and kept anonymous to the database administrator. The database is also password protected, with access only to the administrator and staff members whose IPs have been previously registered in a white list. The research staffs is only provided with read permission to the database.

### Study management

A steering committee has been established to serve as the main governing body of this study. It is composed of cardiologists and clinical research scientists from Shanghai Chest Hospital and epidemiologists from Shanghai JiaoTong University, School of Medicine. The major responsibility of the steering committee is to evaluate, advise on, and approve the study protocol with modifications, communicate with the Ethics Committee, and supervise the practice of community hypertension care in accordance with China’s national hypertension management guideline.

The sponsor of the project is Shanghai Chest Hospital, which is indemnified for any harms as the result of trial participation. A project management team consisting of the principal investigator and the clinical trial operation director has been formed to manage the everyday operation of the study. The operation director is responsible for all decisions on the trial management and intervention delivery.

An independent, external monitor will carry out onsite monitoring, overseen by the study sponsor, once every month at each site following the risk-based monitoring plan established for the study. Safety reporting will follow the safety guidelines of the Project Monitoring Plan, and all adverse events will be recorded in the database.

An Independent Data Monitoring and Safety Committee, consisting of physicians and bioethicists from Shanghai Chest Hospital and statisticians from Shanghai JiaoTong University, School of Medicine, has been established for the trial. This committee is independent from the sponsor and has no competing interests. The committee will be in charge of auditing the trial once every quarter and will meet every 6 months to oversee all ethical and safety issues of the study. The Committee Charter is available from the operation director who manages and coordinates the trial.

